### Procedure for unblinding if needed {17b}

This trial is designed to be double-blinded; however, unblinding will be permitted only in cases where it is necessary for participant safety or when a serious adverse event occurs that requires knowledge of the participant’s group allocation to guide clinical care.

If unblinding is required, the following procedure will be followed:The clinical team responsible for the participant’s clinical management will contact the principal investigator (PI).The PI will review the case and determine if unblinding is necessary.If unblinding is deemed essential, the allocation code will be revealed to the care provider.The unblinding event, reason for unblinding, and any actions taken will be documented in the trial records.

Routine unblinding or revealing of group allocations will not occur unless absolutely necessary for participant safety.

## Data collection and management

### Plans for assessment and collection of outcomes {18a}

The assessment and collection of outcomes, baseline, and other trial data will follow standardized procedures to ensure accuracy and consistency. The primary and secondary outcomes, including pregnancy rates, live birth rates, and embryo survival rates, will be assessed through clinical evaluations, ultrasound examinations, and laboratory testing.

Baseline data will be collected at the time of enrollment, including participants’ age, fertility history, and any relevant medical conditions. These data will be collected using structured case report forms (CRFs), designed to minimize errors and ensure consistency across participants. The CRFs will be attached as part of the study protocol for reference.

Study instruments, such as ultrasound machines for clinical pregnancy assessment and standardized laboratory assays for hCG measurements, will be used. These instruments have been validated for reliability and accuracy in clinical settings.

All data will be recorded in a secure, encrypted electronic database. Regular data audits will be performed to ensure completeness and accuracy.

### Plans to promote participant retention and complete follow-up {18b}

To promote participant retention and ensure complete follow-up, the research team will maintain regular contact with participants through phone calls. Participants will be scheduled for follow-up assessments at specific time points post-embryo transfer, including hCG testing 2 weeks after transfer, ultrasound at 6–8 weeks gestation, and follow-up on pregnancy outcomes such as live birth and birth abnormalities.

For participants who discontinue or deviate from the intervention protocols, efforts will be made to collect all relevant outcome data up until the point of withdrawal. This will include:Reason for discontinuation: collected through phone interviews or in-person discussions.Pregnancy outcomes (if applicable): including any positive or negative pregnancy tests, clinical pregnancy, and live birth outcomes, if the participant is still willing to provide this information.

In cases where participants cannot complete the entire follow-up protocol, efforts will be made to collect as much data as possible from medical records.

### Data management {19}

The study will ensure data integrity and confidentiality through secure and standardized procedures across data entry, coding, storage, and security measures.Data entry: structured CRFs will guide research staff in entering data into a secure, encrypted electronic database. Built-in validation checks will minimize errors, and for critical variables like pregnancy outcomes, double data entry will be implemented to enhance accuracy.Data coding: participants will be anonymized using unique identification numbers. The dataset used for analysis will only contain coded data, with personal identifiers fully removed to protect confidentiality.Data security: strict access controls will be implemented, ensuring that only authorized research personnel can access the data. The encrypted data will be stored on password-protected institutional servers that comply with security standards. Regular data backups will prevent potential data loss.Data storage: data, both physical and electronic, will be securely stored for a minimum of 10 years post-study. Physical consent forms will be kept in locked, secure offices, and electronic data will be encrypted and securely maintained. Personal data will be destroyed according to institutional protocols after the retention period.

### Confidentiality {27}

Personal data of participants will be protected with strict confidentiality throughout the study.Collection: identifiable data, such as contact details and medical history, will be collected during enrollment and kept separate from the anonymized study data. Each participant will be given a unique identification number to ensure anonymity.Sharing: only authorized personnel will have access to identifiable information, and no such data will be shared externally. Any data shared for analysis or reporting will be anonymized to maintain participant confidentiality.Storage: identifiable data will be stored in password-protected, encrypted databases, while physical documents will be securely stored in locked cabinets. Only designated staff will have access to these records.Post-trial: personal data will be stored for a period of 10 years, in line with regulatory guidelines. Once this period has passed, the data will be securely destroyed according to institutional disposal policies.

### Plans for collection, laboratory evaluation, and storage of biological specimens for genetic or molecular analysis in this trial/future use {33}

In this trial, no biological specimens will be collected specifically for genetic or molecular analysis.

## Statistical methods

### Statistical methods for primary and secondary outcomes {20a}

All analyses will follow an intention-to-treat (ITT) approach, with statistical significance set at *p* < 0.05 and 95% confidence intervals (CI). Primary outcomes, including embryo survival rate, pregnancy rate, clinical pregnancy rate, and live birth rate, will be analyzed using logistic regression models, adjusting for potential confounders such as cause of infertility, previous ART cycle, and embryo quality. Chi-square tests or Fisher’s exact tests will be used for categorical outcomes like embryo survival, and logistic regression will report odds ratios (OR) for pregnancy and live birth rates.

Secondary outcomes, including implantation rate and multiple gestation pregnancy rate, will be analyzed using generalized linear models (GLM) and chi-square tests. Thawing time will be compared using *t*-tests or Mann-Whitney *U* tests for non-normal data. Cost-effectiveness will be evaluated through cost-effectiveness analysis (CEA), while post-thaw embryo quality will be assessed using standard grading criteria and analyzed with chi-square tests. Missing data will be handled using multiple imputation to maintain the integrity of the results. An extra sensitivity analysis will be conducted if loss to follow-up is more than 5%.

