**Fig. 1 Fig1:**
[figure not shown]
RCT flowchart

**Table 1 Tab1:** Schedule of the study process

Timepoint	Study period							
	Enrollment	Allocation	Post-allocation					Close-out
	IVF talk	0 week	Embryo transfer	10–14 days	6–8 weeks	20–24 weeks	36–40 weeks	6–8 weeks after birth
Enrollment								
Eligibility screen	X							
Informed consent	X							
Allocation		X						
Interventions								
Administration of different embryo warming methods			X					
Assessments								
Post-thaw embryo assessment			X					
HCG test				X				
Ultrasound of gestation					X			
Phone follow-up						X	X	X

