## Assignment of interventions: allocation

### Sequence generation {16a}

A stratified randomization approach will be used to ensure balanced distribution of participants across treatment groups based on age, a key factor influencing embryo warming and transfer outcomes. Participants will be stratified into two age groups: ≤35 years and >35 years.

Within each age stratum, participants will be randomly assigned to one of two study groups (conventional warming or direct warming) using a computerized randomization process in sealedenvelope.com. Random numbers will be generated for each participant, and participants will be assigned to the intervention or control group randomly, ensuring even distribution across groups within each age stratum.

In the case of an odd number of participants in any stratum, the remaining participant will be randomly assigned to one of the two groups. This method ensures that participants are randomized within each stratum, achieving a balance in age distribution across the treatment groups.

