### Methods for additional analyses (e.g., subgroup analyses) {20b}

Subgroup analyses will be conducted to evaluate the effects of the intervention within predefined groups, such as age (categorized into ≤35 years and >35 years), embryo quality, and cause of infertility. These analyses will help determine if the efficacy of the direct warming method varies across these specific subgroups compared to the conventional multi-step method.

Adjusted analyses will be performed using logistic regression to control for potential confounders, including maternal age, previous IVF cycles, and embryo grading. These adjusted analyses will provide more accurate estimates of the treatment effect on the primary and secondary outcomes.

No additional exploratory analyses are currently planned, though further analyses may be considered based on emerging data trends during the study.

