However, as a multi-center study, the findings may still be influenced by site-specific variations in clinical practices and patient demographics, which could impact generalizability. While the inclusion of multiple centers enhances the study’s external validity, further large-scale trials in diverse settings will be necessary to confirm broader applicability. Additionally, while miscarriage, pregnancy, and live birth rates are primary outcomes, long-term follow-up on birth outcomes, including potential congenital abnormalities, will be crucial to fully assess the safety of this novel method.

This trial protocol is positioned to provide valuable insights into whether the direct warming method can serve as a more efficient and equally effective alternative to conventional multi-step warming. If successful, it could simplify clinical protocols, reduce operational costs, and challenge the traditional understanding of embryo warming processes in ART.

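### The two adjustment lists for the primary outcomes differ, the one in {20a} does not name the age stratum, and neither says whether embryo quality is graded before or after warming

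*Protocol article*

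**What the plan says.** Protocol article, Statistical methods {20a}: the primary outcomes, given there as embryo survival, pregnancy, clinical pregnancy and live birth, are analysed by logistic regression, "adjusting for potential confounders such as cause of infertility, previous ART cycle, and embryo quality". The list is open and names neither age nor centre. The same section compares post-thaw embryo quality between arms by chi-square test, as an outcome.

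Additional analyses {20b}: logistic regression is used to "control for potential confounders, including maternal age, previous IVF cycles, and embryo grading", and this is said to give "more accurate estimates of the treatment effect on the primary and secondary outcomes". Embryo quality is also a subgroup factor there, beside age and cause of infertility.

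Sequence generation {16a}: "Participants will be stratified into two age groups", split at 35 years. No other stratification factor is given. The Discussion says that, through this stratification, age-related differences are taken into account in the analysis.

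On when the embryo is graded:
- Table 1 has one embryo row, "Post-thaw embryo assessment", at the embryo transfer visit, after allocation.
- Section {18a} lists baseline data as age, "fertility history, and any relevant medical conditions". An embryo grade is not named, though the list is not closed.
- The inclusion criteria {10} require at least one good-quality blastocyst, and {11a} sets the threshold at Gardner 3BB or better without saying when the grade is taken.

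**The concern.** Two things are left unsettled in the model that carries the primary conclusions.

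First, the covariate set. Two sections give different lists for the same outcomes and both lists are open. Two analysts could follow the text faithfully and report different odds ratios. The list in the primary section lacks the one factor on which randomisation is stratified, which does not fit the Discussion's statement that age is dealt with in the analysis.

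Second, the timing of the embryo grade. Warming acts on the embryo, so post-warming survival and quality are the natural route by which it could change pregnancy or live birth. A grade taken after warming lies on that route. Adjusting for it, or forming subgroups by it, takes out part or all of the effect under study, and an unmeasured cause of both grade and birth can push the estimate the other way. For embryo survival, which {20a} also models, a post-thaw grade is close to the outcome itself. The stakes are real because the Introduction and Discussion would treat comparable outcomes as success, so a model that shrinks a difference leans towards that conclusion.

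**Working it through.** The plan gives no figure on this point: no live birth rate by arm, grade or age. All rates below are assumptions. Simulations use 550 participants (the plan's 275 per arm) allocated 1:1.

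**1. The two lists side by side**

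| Item | {20a} | {20b} |
|---|---|---|
| Age | not named | maternal age |
| Cause of infertility | covariate | subgroup only |
| Earlier cycles | ART | IVF |
| Embryo | quality, time not stated | grading as covariate and quality as subgroup, time not stated |
| Centre | not named | not named |
| Outcomes covered | primary | primary and secondary |

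**2. If the grade were post-thaw**

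Assume the effect acts wholly through the grade. Then live birth in an arm = P(good) × LBR(good) + P(poor) × LBR(poor).

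*Harm case:* good grade 90% conventional and 75% direct; live birth 45% if good, 15% if poor.
- Conventional: 0.90 × 0.45 + 0.10 × 0.15 = 0.420.
- Direct: 0.75 × 0.45 + 0.25 × 0.15 = 0.375.
- OR = (0.375/0.625) / (0.420/0.580) = 0.83.
- Within each grade the arms have the same rate, so the grade-adjusted OR is 1.00. Simulation (1,500 replicates): 0.83 and 1.00; rejection rate 18% falls to 5%.

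*Benefit case:* good grade 80% conventional and 95% direct; live birth 50% if good, 10% if poor.
- Conventional: 0.80 × 0.50 + 0.20 × 0.10 = 0.420.
- Direct: 0.95 × 0.50 + 0.05 × 0.10 = 0.480.
- OR = (0.480/0.520) / (0.420/0.580) = 1.27. Simulation: 1.28 without the grade and 1.00 with it; rejection rate 30% falls to 6%.

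*Harm case plus an unmeasured common cause* of grade and birth (standard normal, coefficient 1 on both logits): OR 0.86 without the grade, 1.12 with it. The sign reverses.

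A grade recorded before warming cannot be changed by the arm, so none of this applies to it.

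**3. Leaving out the age stratum**

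Analytic check, assuming equal strata with live birth 55% and 30%:
- Mean within-stratum variance = (0.55 × 0.45 + 0.30 × 0.70)/2 = (0.2475 + 0.2100)/2 = 0.2288.
- Total variance = 0.425 × 0.575 = 0.2444.
- Ratio = 0.2288/0.2444 = 0.936, so the unadjusted variance is about 7% too large (1/0.936 = 1.07).
- Actual type I error = 2 × (1 − Φ(1.96/√0.936)) = 0.043.

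Simulation with allocation balanced within stratum (4,000 null replicates; 2,000 replicates with a conditional log OR of 0.5, that is OR 1.65):

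| Control-arm rate by stratum | Type I, age omitted / included | Power, age omitted / included | Mean OR, age omitted / included |
|---|---|---|---|
| 45% / 35% | 5.4% / 5.4% | 82.85% / 84.25% | 1.65 / 1.67 |
| 45% / 25% | 4.9% / 5.4% | 79.1% / 79.6% | 1.61 / 1.65 |
| 50% / 15% | 3.8% / 5.2% | 67.0% / 72.55% | 1.53 / 1.65 |

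The Monte Carlo standard error of a type I error near 5% is √(0.05 × 0.95/4000) = 0.34 points, so 5.4% is compatible with 5%. The power losses are 1.4, 0.5 and 5.55 points. The last column shows that the two lists also estimate different odds ratios once age is strongly prognostic.

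**The case against.** A reader might infer that the primary model does adjust for a post-warming grade. The documents do not support that. Entry requires a good-quality blastocyst, and Table 1 puts the eligibility screen before allocation, so a grade must exist before warming. Section {20a} gives the post-thaw measure its own label when it is an outcome, which suggests that the covariate is something else. Calling the covariate a potential confounder, beside baseline factors, points the same way. Table 1 has no row for any baseline variable, so the absence of a pre-warming grade there proves little. This argument stands in full against the strong reading. It does not settle the timing, which no section states, while the only scheduled assessment is the post-thaw one.

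It can also be said that laboratory harm would show anyway, because survival and post-thaw quality are compared directly. That is so, but those comparisons would not repair a distorted estimate for pregnancy or live birth.

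A reader might further infer that age is ignored. It is not: {20b} adjusts the primary outcomes for maternal age, and the {20a} list is open. What remains is an inconsistency.

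Nor does the missing centre term make the standard errors wrong in the way a missing stratum does. Centre is not a randomisation stratum, so no balance is forced within it. The Discussion concedes that "the findings may still be influenced by site-specific variations in clinical practices and patient demographics", but with individual 1:1 randomisation, omitting centre leaves the test valid and costs at most some efficiency.

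Finally, the complete disappearance of the effect in the examples follows from assuming full mediation. With partial mediation and no common cause, only part would be lost.

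**Conclusion.** The point holds as a problem of consistency and definition. {20a} and {20b} do not fix one model for the primary outcomes, and the list in {20a} omits the only stratification factor. That can be read from the text without assumptions.

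The embryo-quality part is an unresolved ambiguity, not a proven adjustment for a post-randomisation variable. If it were resolved the wrong way, an effect on pregnancy or live birth could be hidden (OR 0.83 to 1.00) or reversed (0.86 to 1.12). Those sizes depend on the assumed rates and, for the first, on full mediation.

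The age part is small and errs on the safe side. Type I error is at or slightly below nominal. The power loss is about 1 point at modest age effects and about 6 points at strong ones, assuming equal strata and allocation balanced within them. It does not threaten the validity of the trial. The correction is worth making because it costs almost nothing and brings the analysis into line with the randomisation.

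**What to change.** - Give one closed covariate list in {20a} and use the same list in {20b}. Include the age stratum (or continuous age) and the Gardner grade recorded before warming.
- Name that pre-warming grade among the baseline data in {18a}, and use it wherever embryo quality defines a subgroup.
- State that no post-thaw measure enters any efficacy model or subgroup. Post-thaw quality stays as an outcome.
- Adjusting for centre is optional, for efficiency. If it is done, say how small centres are handled, since the number of centres is not yet settled.

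The cost is a few sentences and one case report form field for a grade that the inclusion criterion already requires. The sample size and randomisation do not change.

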### Interim analyses {21b}

Given the multi-center nature of this study and the established safety profile of the intervention, no formal Endpoint Adjudication Committee (EAC) or Data Monitoring Committee (DMC) will be established. Instead, the oversight responsibilities for interim analyses and stopping guidelines will be managed by the Trial Steering Committee (TSC).

An interim analysis will be conducted when 50% of the anticipated sample size has been completed, or midway through the trial if any significant safety concerns or deviations from expected outcomes arise. The TSC will review interim results and decide whether to continue, modify, or terminate the trial based on predefined stopping criteria, including serious adverse events directly resulting from the intervention and clear evidence of futility or overwhelming efficacy, such as a 10% embryo survival rate lower than the conventional group. The study team will remain blinded, with only TSC members having access to interim data to ensure unbiased trial conduct.

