### Sample size {14}

The sample size calculation was based on preliminary data indicating approximately a 5% increase in the live birth rate with the new method compared to conventional warming. With type I error (*α*) set at 0.05 and type II error (*β*) set at 0.2 (80% power), and assuming a clinically significant difference of 20% in the worldwide clinical pregnancy rate, the required sample size per arm is 275, calculated using MedCalc 15.6.1. To account for a 5% loss to follow-up, a total of 578 participants will be enrolled (289 per arm). Given that the total number of participating centers is currently undetermined, the leading center, IVFHK-CUHK, will serve as the core recruitment site. This center can independently recruit at least 578 participants.

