## Oversight and monitoring

### Composition of the coordinating center and trial steering committee {5d}

The coordinating center for this trial is based at IVFHK-CUHK, which will oversee the day-to-day management of the study across all participating sites, including CUHK Medical Centre and the HEAL Fertility. The coordinating center is responsible for protocol implementation, site coordination, data collection, monitoring, and regulatory compliance. It will provide logistical and administrative support to ensure adherence to study procedures and timelines. It consists of a trial manager (oversee the entire trial operation, monitor performance indicators, and communicate with other bodies), regulatory specialist (manage and monitor all regulatory documents including ethics application and renewal, protocol amendments, and other reports), site coordinators (communicate with individual centers, especially about the standard procedures), research nurses (provide clinical oversight and review medical records of the participants), and data coordinators (data collection, entry, and storage). The coordinating center will hold regular meetings (at least quarterly) to review trial progress and address operational challenges.

The TSC will provide oversight, ensuring the trial adheres to the study protocol and relevant regulations. The TSC will meet biannually to assess study progress, review interim data if needed, and discuss any protocol deviations or necessary amendments. The TSC comprises an independent chairperson, clinical experts in obstetrics and gynecology, a statistician, an ethics advisor, and the principal investigator. Most members are independent, ensuring objective oversight of the trial.

The Data Management Team, integrated within the coordinating center, will oversee data entry, coding, and storage, ensuring the accuracy and security of the data.

No additional committees, such as an endpoint adjudication committee or data monitoring committee, are planned. The study team and the TSC will collectively handle oversight of key outcomes and adjudication, as needed.

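### The principal investigator sits on the only committee that sees interim data, the futility/efficacy criterion is illustrated by a harm signal, and the efficacy stop has no stated allowance in alpha

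*Protocol article*

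**What the plan says.** All references are to the protocol article.

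- **Who sees interim data.** Interim analyses {21b}: "The study team will remain blinded, with only TSC members having access to interim data". The same section lets the TSC continue, modify or terminate the trial on that basis. Composition of the coordinating center and trial steering committee {5d} ends its list of TSC members with "a statistician, an ethics advisor, and the principal investigator", and adds that most members are independent. Sections {5d}, {21a} and {21b} all say that no data monitoring committee will be set up.
- **Stopping criteria.** {21b} calls the criteria predefined. It names serious adverse events caused by the intervention, and then "clear evidence of futility or overwhelming efficacy, such as a 10% embryo survival rate lower than the conventional group". That 10% is the only number in the criteria.
- **Status of embryo survival.** Statistical methods {20a} counts it among the primary outcomes. The primary list in Outcomes {12} does not. The secondary list in {12} mentions it only within the comparison of warming-media brands.
- **Significance level.** {20a}: "All analyses will follow an intention-to-treat (ITT) approach, with statistical significance set at" p < 0.05. Sample size {14} uses a type I error of 0.05 and 80% power and mentions no interim look.

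**The concern.** Three separate weaknesses meet in one short section.

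First, the firewall fails on the protocol's own terms. With no monitoring committee, the TSC is the only barrier between interim results and the people running the trial, and the principal investigator is on both sides of it. Knowledge gained at the look cannot be taken back. It could colour decisions to modify the trial, and {20b} leaves room for further analyses prompted by emerging data trends.

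Second, a committee cannot apply a criterion consistently when its only worked example points the wrong way for one of the two things it is meant to illustrate.

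Third, a trial intended to support adoption of a new method may stop early for efficacy, yet the protocol does not say how strong the evidence must be, on which outcome, or what remains for the final test.

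**Working it through.** **1. Access to interim data: the sections side by side.**

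- {21b}: the study team stays blinded; only TSC members see interim data.
- {5d}: the principal investigator is a TSC member.
- {17b}: the principal investigator decides on unblinding requests from the clinical team. The Data Availability section gives the principal investigator access to the final dataset alongside the analysis team. The role plainly belongs to the study team.

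The first two statements cannot both hold. Coding the arms would not rescue them: a criterion that asks whether survival is lower than with conventional warming can be applied only by someone who knows which arm is which.

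**2. The stopping example.**

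- Direction: lower survival than conventional is unfavourable to direct warming. It cannot illustrate overwhelming efficacy. It is a harm signal, or loosely a futility signal.
- Scale: no survival rate for conventional warming is given. Assume 95% to 99%. An absolute reading of 10% puts the limit at 95 − 10 = 85% to 99 − 10 = 89%. A relative reading puts it at 0.9 × 95 = 85.5% to 0.9 × 99 = 89.1%. At high survival the two readings differ by half a point or less, so this ambiguity is a wording defect more than a large numerical one.
- Outcome status: primary in {20a}, absent from the primary list in {12}, and present in {12} only under a secondary media comparison.

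**3. The plan's own sample-size figure.**

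{14} goes from 275 per arm to 578: 275 × 1.05 = 288.75, rounded up to 289, and 2 × 289 = 578. The only inflation is for 5% loss to follow-up. The 275 cannot be fixed from the stated inputs because no control rate is given. If the 20% is read as relative, a fixed-sample two-sided calculation returns 275 at an assumed control rate of about 57.5%, with no interim adjustment. The type I error result below does not depend on this.

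**4. Type I error with two looks.**

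Inputs: one look at half the information ({21b}) and one at the end; final test at two-sided 0.05 ({14} and {20a}; two-sided is an assumption, as sidedness is not stated); one outcome.

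Under no difference, Z₁ and Z₂ are standard normal with correlation √0.5 = 0.707. Overall error = 1 − P(|Z₁| < c₁ and |Z₂| < c₂).

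| Interim rule | c₁ | c₂ | Overall two-sided error |
|---|---|---|---|
| p < 0.05 | 1.960 | 1.960 | 0.0831 |
| p < 0.001 | 3.2905 | 1.960 | 0.0502 |

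A simulation of 1,000,000 trials gave 0.0826 for the first row. The range is therefore about 5.0% to 8.3% per outcome: an excess over 5% of between 0.02 and 3.3 percentage points, depending on a rule that the protocol does not state.

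Two-look plans that hold 0.05 exactly: O'Brien-Fleming, interim p < 0.0052 and final p < 0.0480; Lan-DeMets spending of O'Brien-Fleming type, 0.0056 and 0.0478; Pocock, 0.0294 at both looks.

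**The case against.** **Boundaries belong in an analysis plan.** {21b} calls the criteria predefined, its list need not be complete, and only a condensed article is shown. The p < 0.05 in {20a} can be read as the level for the final analysis. This stands in large part. A reader might infer that the trial as written runs at 8.3%. The documents do not support that: nothing says the interim is judged at 0.05, and the word overwhelming points to something stricter. What remains is that an efficacy stop is expressly permitted while the stated 0.05 is fully used elsewhere. The alpha point is therefore conditional.

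**Several primaries make it worse.** A reader might infer that the interim look multiplies the error across all clinical primaries in {12}. Testing several primaries raises the error at the final analysis even without an interim. That is a separate matter, and its size depends on event rates and correlations that the documents do not give.

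**Embryo survival.** A reader might infer that it is not an outcome in {12} at all. It is, under the secondary media comparison. The inconsistency is only about whether it is primary. The intended sense of the example, that worse survival should raise the question of stopping, can also be guessed. But a stopping criterion should not have to be guessed.

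**Independence of the TSC.** The chair is independent, as are most members, and {17a} separately blinds participants, the clinical team, outcome assessors and analysts. A reader might infer that the principal investigator's seat destroys the trial's blinding. It does not: those safeguards remain, and the main clinical endpoints are ultrasound findings or births. Likewise, the emergency unblinding role in {17b} is a separate function and gives no access to comparative results. None of this removes the contradiction between {21b} and {5d}, because a majority of independent members does not blind the one who is not.

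**Conclusion.** The concern holds in three parts of unequal strength.

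1. **Access to interim data: firm.** {21b} and {5d} contradict each other. Followed as written, the plan shows interim results to the principal investigator, who then takes part in deciding the trial's course. This rests on the text alone, and an analysis plan would not normally settle committee membership.
2. **Stopping example: firm as an error of wording.** The example cannot illustrate efficacy, the 10% is not defined as absolute or relative, and the outcome's status differs between {12} and {20a}. No view is taken here on what the threshold should be.
3. **Alpha: conditional.** Per-outcome two-sided type I error is about 5.0% to 8.3%, assuming one look at half the information and a final test at 0.05. The upper end applies only if the interim is judged at nominal 0.05. If an analysis plan not shown already sets a boundary, this part is answered.

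The first part must be settled before the half-way look, since blinding lost there cannot be restored.

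**What to change.** - **{21b} and {5d}:** state that interim data by arm are reviewed in a closed session of the independent TSC members and the statistician, with the principal investigator excluded until database lock. Cost: the principal investigator misses that session. No new committee is needed.
- **{21b}:** list the harm criterion separately from futility and efficacy. The sponsor must reconcile the 10% wording, say whether it is absolute or relative, and align the status of embryo survival between {12} and {20a}. Cost: a few sentences.
- **{21b} and {20a}:** unless an analysis plan already sets a boundary, either remove efficacy stopping, which leaves the final test at 0.05, or state a stringent boundary on one named efficacy outcome. Haybittle-Peto (interim p < 0.001, final test at 0.05) is one example: overall error is 5.02%, with essentially no loss of power because the final test is unchanged. O'Brien-Fleming would hold 5% exactly, with a final level of 0.0480. The cost here is more than wording: {12} lists five primary measures, so the protocol must first designate the outcome to which the boundary applies.
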